## Abstract

**Background:**

Approximately 2 million patients present to emergency departments in the USA annually with signs and symptoms of ureterolithiasis (or *renal colic*, the pain from an obstructing kidney stone). Both ultrasound and CT scan can be used for diagnosis, but the vast majority of patients receive a CT scan. Diagnostic pathways utilizing ultrasound have been shown to decrease radiation exposure to patients but are potentially less accurate. Because of these and other trade-offs, this decision has been proposed as appropriate for Shared Decision-Making (SDM), where clinicians and patients discuss clinical options and their consequences and arrive at a decision together. We developed a decision aid to facilitate SDM in this scenario. The objective of this study is to determine the effects of this decision aid, as compared to usual care, on patient knowledge, radiation exposure, engagement, safety, and healthcare utilization.

**Methods:**

This is the protocol for an adaptive randomized controlled trial to determine the effects of the intervention—a decision aid (“Kidney Stone Choice”)—on patient-centered outcomes, compared with usual care. Patients age 18–55 presenting to the emergency department with signs and symptoms consistent with acute uncomplicated ureterolithiasis will be consecutively enrolled and randomized. Participants will be blinded to group allocation. We will collect outcomes related to patient knowledge, radiation exposure, trust in physician, safety, and downstream healthcare utilization.

**Discussion:**

We hypothesize that this study will demonstrate that “Kidney Stone Choice,” the decision aid created for this scenario, improves patient knowledge and decreases exposure to ionizing radiation. The adaptive design of this study will allow us to identify issues with fidelity and feasibility and subsequently evaluate the intervention for efficacy.

**Trial registration:**

ClinicalTrials.gov NCT04234035. Registered on 21 January 2020 – Retrospectively Registered

**Supplementary Information:**

The online version contains supplementary material available at 10.1186/s13063-021-05140-9.

## Administrative information

The order of the items has been modified to group similar items (see http://www.equator-network.org/reporting-guidelines/spirit-2727-statement-defining-standard-protocol-items-for-clinical-trials/).

## Introduction

### Background and rationale {6a}

Ureterolithiasis is common, painful, and costly, but usually self-limited. Every year, emergency departments (EDs) in the USA see over 2 million patients presenting with signs and symptoms of ureterolithiasis [1, 2]. Although the pain from passing a kidney stone is known to be severe, less than 1 in 5 of patients with confirmed stones will require urologic intervention over the course of their disease process, as most kidney stones pass spontaneously within several weeks [2–4].

The gold standard for the diagnosis of ureterolithiasis is non-contrast CT scan—both for its accuracy in diagnosing ureterolithiasis and its ability to pick up dangerous alternative diagnoses [5]. However, over the past decade, evidence suggesting that routine use of CT for the diagnosis of uncomplicated (non-infected) kidney stones is unnecessary has mounted. First, the rate of serious alternative diagnoses is lower than previously believed when older patients and patients with clinically apparent risk factors are excluded [6, 7]. Second, a risk score that stratifies patients based on the likelihood that their pain is caused by a kidney stone, the STONE score, has been developed and externally validated [8, 9]. Use of the STONE score improves clinicians’ pre-test probability for kidney stones and informs the use of ultrasound (US) as a diagnostic alternative to CT [8, 9]. Third, a multicenter randomized controlled trial demonstrated that an US-first algorithm is as safe as a CT-first algorithm and resulted in lower cumulative radiation to patients [10].

While the superior accuracy of CT is not debatable, concerns regarding lifetime radiation exposure have led many to propose alternative diagnostic algorithms [11–13]. Many patients with kidney stones undergo two or more CT scans during the management of each unique episode of colic; fluoroscopy is often used during the treatment of stones; and recurrent episodes of colic, which occur in > 50% of patients, result in repeat imaging [14, 15]. The medical literature demonstrates clearly that patients often do not understand that they are being exposed to ionizing radiation or that this exposure may increase their future risk of cancer [16]. Emergency physicians report a desire to convey this information, but are also not always correct in their own understanding of the risks of radiation [16].

As the decision of whether to utilize CT scanning in the diagnosis of ureterolithiasis has trade-offs involving radiation, accuracy, cost, and time spent in the ED, many feel that it is appropriate for shared decision-making [17]. Shared Decision-Making (SDM) is a process by which clinicians share the risks and benefits of the options and the patients share their values and preferences, and together come to a decision [18].

### Objectives {7}

In this paper, we describe the rationale and methods used to design and test the feasibility and efficacy of the Kidney Stone Choice decision aid in a randomized controlled trial. We hypothesize that the use of the decision aid will significantly increase patient knowledge and engagement and decrease radiation exposure for this population.

### Trial design {8}

This pragmatic, adaptive randomized controlled trial compares an intervention group receiving a structured, risk-stratified decision aid, “Kidney Stone Choice (KSC),” to a control group receiving usual care [19]. IRB approval has been obtained and the trial has been registered at www.ClinicalTrials.gov (NCT04234035). Trial design is based on the theoretical model in Fig. 1: we hypothesize that the KSC decision aid may directly decrease CT scan usage via its effects on providers, or may decrease CT scan usage via Shared Decision-Making’s effects on knowledge, trust, and patient engagement. The adaptive design is explained in Outcomes {12}, Sample size {14}, and Fig. 3.

**Fig. 1 Fig1:**
[figure not shown]
Theoretical model for study design and outcome selection

#### Decision Aid Development

Using evidence-based stakeholder engagement methods, we developed a decision aid (KSC) to facilitate SDM in the scenario of suspected ureterolithiasis [20]. The initial decision aid was developed and beta-tested in a single-center decision-aid development study at Baystate Medical Center, Springfield, MA, USA, and details of this process have been previously published [20]. Development of the decision aid iteratively involved patient and clinician stakeholders and resulted in a tool that meets International Patient Decision Aid Standards [21, 22]. The refined 6-page decision aid is available as Supplementary material 1.

Pilot testing demonstrated both feasibility and acceptability in 10 clinician-patient dyads. The decision aid is designed to facilitate, not replace, a conversation between the clinician and the patient. It describes the decision at hand, background information about kidney stones that both clinicians and patients felt was important, and the risks and benefits of the two options (“Wait and see” or “CT before going home”). The goals of the decision aid are to increase patient knowledge about the risk of radiation, increase patient engagement in decision-making, and decrease radiation burden in this population.

## Methods: Participants, interventions, and outcomes

### Study setting {9}

Patients and clinicians will be recruited from the emergency department at Baystate Medical Center in Springfield, MA, USA. This ED sees > 115,000 visits per year, and is staffed by board-certified Emergency Physicians, advanced practitioners, and emergency medicine residents. The trial will be conducted within the flow of routine patient care.

### Eligibility criteria {10}

Eligible patients will include adults age 18–55 presenting to the ED with a chief complaint of flank pain who are being considered by the treating clinician for a CT scan for the diagnosis of ureterolithiasis. Exclusion criteria are listed in Fig. 2. Data will be collected on all patients assessed for eligibility and we will report the number of excluded patients, the rationale for each exclusion, and the number of patients who decline consent to participate in the study in accordance with the CONSORT guidelines for reporting randomized trials [23]. Participants with and without a history of ureterolithiasis will be eligible, but the intervention will be tailored to their history. Eligibility criteria were determined by stakeholder engagement during the process of decision aid development [20].

**Fig. 2 Fig2:**
[figure not shown]
Flow diagram showing the integration of study procedures in the flow of patient care

### Who will take informed consent? {26a}

A study coordinator will identify potentially eligible patients based on the chief complaint and, in collaboration with the treating clinician, confirm patient eligibility for the trial (Fig. 2). The study coordinator will then obtain written informed consent from the patient. Verbal consent will be obtained from participating clinicians at the time of patient consent—if clinicians agree to be recorded. Patients will be consecutively enrolled five to seven days per week whenever a study coordinator is available for enrollment.

Consent for audio recordings will be separate from the consent for the trial and lack of consent for recording will not preclude participation in the trial. Clinicians will verbally consent to recording as well—if either the patient or the clinician does not consent, the conversation will not be recorded. If no conversation takes place regarding diagnostic options, a recording will not be made.

#### Integrating patient recruitment, consent, and delivery of the intervention in the flow of patient care

Figure 2 shows how the process of patient recruitment, consent, randomization, and delivery of the intervention will integrate with the flow of patient care. We will assess patient eligibility and obtain consent shortly after the clinician has evaluated the patient, treated their pain, and begun diagnostic testing (but prior to ordering a CT scan). Patients will then be randomized and receive the intervention or usual care. Patients for whom an exclusion criterion becomes apparent post-randomization (ex. patient who develops a fever, has a positive pregnancy test, or is found to have a solitary kidney on ultrasound) will be classified as screen failures and not analyzed [24].

Patients who are randomized to the decision aid arm will then be given the decision aid, and the clinician will be prompted to discuss the diagnostic options. For the purposes of blinding, patients randomized to usual care will receive a paper informational sheet and the clinician will be prompted to proceed with usual care regarding diagnostic imaging.

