##### Certainty (“risk”) assessment and delivery of the intervention

The study coordinator will collect pre-intervention variables from patients, including the components of the STONE score [8]. The coordinator will collect and collate relevant variables from the clinician, including ultrasound results. The clinician will receive a document clarifying the patient’s STONE score and the meaning of that score (Ex. Moderate STONE score + mild hydronephrosis = 90% chance of stone) (see Supplementary Material 2). The study coordinator will then provide the clinician with a color copy of the decision aid to provide a concise refresher of the content. There are two areas of the decision aid where the clinician will be prompted to enter data personalized to the patient. First, they will be prompted to fill in a line about pre-test probability, based on the STONE Score and the ultrasound results. Second, they will be given the option of indicating their recommendation prior to the conversation. The decision aid will then be given to the patient, and the study coordinator will give the patient at least 15 min to read the decision aid prior to discussion with the clinician. The treating clinician will then, using the KSC decision aid as a tool to facilitate a conversation, educate the patient regarding the rationale for their clinical suspicion up to that point in the ED visit and engage the patient in a shared decision regarding whether to obtain a CT at that time.

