### Criteria for discontinuing or modifying allocated interventions {11b}

The patient or treating clinician may withdraw from the trial at any time. The treating clinician may engage in Shared Decision-Making without accessing the decision aid (if in the usual care arm) or may not engage in Shared Decision-Making despite the use of the decision aid (if in the intervention arm). Subjects for whom an exclusion criteria becomes apparent after randomization (such as a new onset fever or newly discovered pregnancy) will be excluded from analysis and further study procedures and considered screening exclusions.

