#### Multivariable analyses

We will apply ICH-E9 guidelines for statistical analysis and the CONSORT statement for reporting of findings for clinical trials [31, 34]. For multivariable analyses, linear regression or logistic regression will be used to adjust for baseline characteristics that do not appear to be balanced upon inspection or show moderate to large standardized effect sizes. Covariates that do not meaningfully modify estimates of treatment effect or otherwise contribute to clinical interpretation may be removed from the final model.

In multivariable models, we will assess for heterogeneity of treatment effects by including interaction terms (specifically, age, gender, and race/ethnicity, insurance, education, and health literacy) with treatment group [35]. In view of our limited sample size to detect significant interaction terms, we will consider any interaction term as worthy of further evaluation if significance testing achieves a critical test level of 0.15.

Our primary analyses will proceed via an intention-to-treat approach, as some cross-over is expected. All measures of treatment effects (e.g., odds ratios, difference in means or proportions) as well as estimates of group specific effects (e.g., means and proportions) will be reported with 95% confidence intervals. However, patients with exclusion criteria that manifest post-randomization will NOT be included (ex. pregnancy diagnosed in the ED).

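### Randomised patients who meet an exclusion criterion after allocation, new-onset fever included, are dropped from analysis and follow-up under an intention-to-treat label, so some of the patients with safety events could go uncounted

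*Protocol article*

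**What the plan says.** The protocol article states the rule in three places.

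- **Integrating patient recruitment, consent, and delivery of the intervention in the flow of patient care.** Randomisation comes first: "Patients will then be randomized and receive the intervention or usual care". A patient in whom a ground for exclusion "becomes apparent post-randomization (ex. patient who develops a fever, has a positive pregnancy test, or is found to have a solitary kidney on ultrasound" is then treated as a screen failure and left out of the analysis, with a reference cited.
- **Criteria for discontinuing or modifying allocated interventions {11b}.** Where a criterion "becomes apparent after randomization (such as a new onset fever or newly discovered pregnancy", the patient "will be excluded from analysis and further study procedures and considered screening exclusions". Follow-up therefore stops as well.
- **Multivariable analyses.** "Our primary analyses will proceed via an intention-to-treat approach, as some cross-over is expected". The same paragraph adds the exception that "patients with exclusion criteria that manifest post-randomization will NOT be included (ex. pregnancy diagnosed in the ED".

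Under Who will be blinded {17a}, clinicians and study staff are unblinded. Outcomes {12} names HRDwC, as a marker of missed or delayed diagnosis, among the safety outcomes. Adverse event reporting and harms {22} counts hospital admission for antibiotics as a serious adverse event and collects adverse events at scheduled follow-up.

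**The concern.** An intention-to-treat comparison is protected because nothing that happens after allocation can change who is counted. Here something can. A positive pregnancy test or a solitary kidney usually reveals a state that existed before randomisation. Section {11b} also names fever of new onset, which can be an event of the trial itself. The population is meant to have uncomplicated (non-infected) stones, and the choice under study is whether to have a CT before going home. Fever in such a patient may be the first sign of a complication that the safety outcomes exist to capture.

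Two things are at stake. The first is the safety comparison: a patient who becomes febrile and is admitted for antibiotics meets the serious adverse event definition and, on the same facts, is a screening exclusion whose study procedures end. The study pause in {21a} is triggered by three related serious events, so a single uncounted one is not trivial. The second is the CT comparison, which becomes conditional on an exclusion decision that staff make knowing the arm.

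**Working it through.** **1. The passages side by side.** The three statements agree on removal from analysis; {11b} adds the end of study procedures. None of them:

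- sets a time limit;
- requires that the criterion existed before randomisation;
- requires a decision made without knowledge of arm;
- keeps these patients for safety.

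The hospital-record search for HRDwC in {18b} is described only for participants lost to follow-up. Contacts that were never made at 2 and 8 weeks cannot be restored at analysis.

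**2. The plan's own power figure.** Inputs from Sample size {14}: 80% v 60% CT use, 100 per arm, alpha 0.047 (two-sided per {21b}, z = 1.986). With pooled variance:

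power = Φ[(0.20·√n − 1.986·√(2·0.7·0.3)) / √(0.8·0.2 + 0.6·0.4)]

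At n = 100: Φ[(2.000 − 1.287)/0.632] = 0.870, the stated 87%. Assumed exclusions of 2%, 5% and 10% leave 98, 95 and 90 per arm and power of 0.863, 0.852 and 0.833. Loss of power is therefore a minor matter.

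**3. Bias in CT use.** Assume no true effect, with 80% CT use among all randomised patients in each arm. Let e be the fraction excluded.

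- If every excluded patient had a CT, the observed proportion is (0.8 − e)/(1 − e).
- If none did, it is 0.8/(1 − e).

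The exclusion rates below are assumptions, since the documents give none. Differences are aid minus usual care.

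| Excluded, aid v usual care | All excluded had a CT | None had a CT |
|---|---|---|
| 5% v 5% | 0.7895 − 0.7895 = 0 | 0.8421 − 0.8421 = 0 |
| 5% v 2% | 0.7895 − 0.7959 = −0.6 points | 0.8421 − 0.8163 = +2.6 points |
| 10% v 2% (an extreme case) | 0.7778 − 0.7959 = −1.8 points | 0.8889 − 0.8163 = +7.3 points |

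By the normal approximation, the type I error at 5% v 2% moves from 0.047 to 0.048 (all had a CT) or 0.072 (none did). The sign depends on CT use among the excluded, which the documents do not give.

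**4. Safety counts.** No HRDwC rate is given. With an assumed 0.5% to 2%, the expected number in 200 patients is 200 × 0.005 = 1 to 200 × 0.02 = 4. If one removed patient were an HRDwC case, that would be a quarter or more of the expected total.

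**The case against.** The best defence is that the rule is open and consistent. The exception directly qualifies the intention-to-treat statement, a reference is cited, and Eligibility criteria {10} promises the number of exclusions and the reason for each. That stands: this is a declared modification under a loose label, not a hidden contradiction.

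The context also points to the index visit. The rule is stated before the aid is handed over, the patients are called screening exclusions, and one example is a pregnancy found in the ED. That is a fair reading, and nothing supports taking the rule as running to day 60. It does not remove the problem. No limit is written, and {22} counts admission at enrolment as an adverse event, so even a fever on day 0 could be both a safety event and an exclusion. Blinding the follow-up assessor does not help, because the exclusion can be made earlier.

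The Data Safety Monitoring Plan (Supplementary Material 6) is not shown and may retain these patients for safety. If it does, {11b} must be made to agree with it.

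Two stronger readings are tempting and are not supported:

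- **That the rule removes the patients with missed diagnoses in general.** It reaches only those who meet a listed criterion. A patient sent home without CT and later found to have another diagnosis stays in unless that event is on the list. The list in Fig. 2 and the HRDwC definition are not shown, so only *some of the patients* can be claimed.
- **That a solitary kidney is found more often in the aid arm because the aid uses ultrasound.** The clinician is told "they will be prompted to fill in a line about pre-test probability, based on the STONE Score and the ultrasound results", but this uses results already collected and orders no scan. Testing begins before consent in everyone, and usual care may include ultrasound or CT. Neither a difference in detection nor its direction is shown.

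**Conclusion.** The concern holds in a limited form. As written, the plan drops randomised patients for events that can arise after allocation, lets unblinded staff identify them, and ends their follow-up. New-onset fever is the clear case; pregnancy and solitary kidney are defensible exclusions if judged blind to arm.

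The main exposure is the safety comparison. Its size cannot be computed without fever, exclusion and HRDwC rates, but with the assumed 1 to 4 HRDwC in 200 patients, one lost event matters. For CT use, the bias at an assumed 5% v 2% lies between -0.6 and +2.6 points against a 20-point target, and it is zero with balanced exclusions and equal CT use among the excluded. A reader might infer that the rule favours the aid; the range includes both signs, so the documents do not support that.

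**What to change.** Amend the three sections together:

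1. Follow all randomised patients to day 60 and include them, in the arm assigned, for safety and utilisation outcomes.
2. Do not exclude for an event that arises after randomisation.
3. Allow exclusion from the CT and knowledge analyses only for criteria that objectively predate randomisation, judged by someone who knows neither arm nor outcome.
4. Report counts and reasons by arm.
5. Present an analysis of all randomised patients alongside, or call the restricted set modified intention-to-treat.

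Forcing patients who were ineligible from the start into the primary CT analysis is more debatable, and this fix does not require it.

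The cost is revised wording in three sections, follow-up of probably a few more patients, a blinded eligibility check, and slight dilution of the CT effect from patients for whom imaging was no longer a choice.

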## Interventions

### Explanation for the choice of comparators {6b}

This study compares a decision aid designed to facilitate Shared Decision-Aid with “Usual Care,” operationalized as a standard information sheet about nephrolithiasis. Decision aid development has been published previously [20].

### Intervention description {11a}

#### Intervention arm

##### Training

Trainings for practicing clinicians will be provided both via a one-hour lecture prior to the start of the trial and a 3-min “just in time” refresher will be administered just before the SDM conversation. All practicing clinicians will be invited to participate.

